## Abstract

**Background:**

Approximately one in four pregnant women undergo an induction of labour. The purpose of this study is to investigate the clinical effectiveness, safety, and cost-effectiveness for mothers and babies of two methods of cervical ripening – inpatient care for women starting induction with vaginal prostaglandin E2 hormones, or allowing women to go home for 18 to 24 h after starting induction with a single-balloon catheter.

**Methods/design:**

This is a multi-centre randomised controlled trial in New Zealand. Eligible pregnant women, with a live singleton baby in a cephalic presentation who undergo a planned induction of labour at term, will be randomised to outpatient balloon-catheter induction or in-hospital prostaglandin induction. The primary outcome is caesarean section rate. To detect a 24% relative risk reduction in caesarean rate from a baseline of 24.8%, with 80% power and 5% type 1 error, will require 1552 participants in a one to one ratio.

**Discussion:**

If outpatient balloon-catheter induction reduces caesarean section rates, has additional clinical benefits, and is safe, cost-effective, and acceptable to women and clinicians, we anticipate change in induction of labour practice around the world. We think that home-based balloon-catheter induction will be welcomed as part of a patient-centred labour-induction care package for pregnant women.

**Trial registration:**

Australia New Zealand Clinical Trials Registry (ANZCTR), ACTRN: 12616000739415. Registered on 6 June 2016.

## Background

### Introduction

Induction of labour (IOL) is a common intervention in childbirth. Globally, approximately one in four pregnant women undergo an IOL, with significant variation by country [1]. IOL is defined as the artificial initiation of labour [2]; the alternative is expectant management of the pregnancy where spontaneous labour is awaited. IOL is offered when evidence shows that the benefit to mother and/or baby of an earlier planned birth outweighs the risks of induction. Common clinical scenarios for IOL include women with pre-labour rupture of membranes, or whose pregnancy is more than 1 week beyond their expected due date.

In New Zealand (NZ), the proportion of women who undergo an IOL has steadily increased, from 19.4% in 2006 to 24.0% in 2015 [3]. Compared to spontaneous onset of labour, IOL is associated with a prolonged length of hospital stay and with increased rates of epidural insertion, caesarean section, and post-partum haemorrhage. IOL has an impact on the woman’s experience of labour and birth, with women having to reconsider their birth plans and in some cases their planned place of birth. Women have identified that more pain relief during labour is required, they feel less positive about their birth experience and find the induction process challenging [4–6]. IOL also has an impact on hospital and staff resources, with a significant occupancy of acute beds and allocation of clinical resources for the obstetric unit. There is the potential for service commitments of IOL care to impact on the safe and efficient care to other women accessing acute maternity and gynaecological care.

In NZ, most women have their induction commenced with pharmacological methods. The most common method of cervical ripening (making the cervix ready for induction) involves one or more doses of prostaglandin (PG) E2 gel inserted into the vagina at regular intervals or a PGE2 controlled-release pessary that is inserted into the vagina and remains in situ for 12–24 h. This is followed by artificial rupture of membranes (breaking the waters) (ARM) and an intravenous infusion of oxytocin to stimulate uterine contractions. The vast majority of women will remain in hospital throughout. Prostaglandins (PGs) for cervical ripening are associated with the complication of uterine hyperstimulation (defined as contractions every minute or two or contractions lasting longer than 2 minutes, and associated with fetal distress; reported to occur about 5% of the time) [7].

### Literature review

There is moderate-quality evidence that mechanical methods (such as a balloon catheter) are a safe and effective alternative to pharmacological methods to ripen the cervix and induce labour. The Cochrane review on mechanical methods included 17 randomised controlled trials (RCTs) (1894 women) comparing IOL with mechanical methods to PGs [8]. Women undergoing IOL with a balloon catheter had less uterine hyperstimulation (0% vs 5%, risk ratio (RR) 0.16 (0.06–0.39)), and fewer instrumental vaginal births (21% vs 27%, RR 0.79 (0.64–0.98)). Balloon-catheter inductions were associated with more oxytocin usage (75% vs 50%). Both methods had comparable rates of vaginal birth not achieved within 24 h (RR 1.97 (0.43–8.95)), and of caesarean section (26% vs 23%, RR 1.07 (0.91–1.25)).

Diederen et al. performed a meta-analysis of 26 studies (8292 women) who had undergone cervical ripening with a balloon catheter [9]. The most common adverse event was participant pain/discomfort, which occurred in 3 in 1000 participants. This study suggests that the risk of adverse events, such as uterine hyperstimulation, during the period between insertion and expulsion of a balloon catheter in cervical ripening is very low (ranging from 0.0 to 0.26%). The authors concluded that further evaluation and implementation of this procedure in an outpatient setting for low-risk pregnancies was needed.

There is low-quality evidence that outpatient care during the cervical ripening phase of IOL is an alternative to inpatient care. The Cochrane review included four RCTs comparing outpatient to inpatient labour induction [10]. Three used PGs; one used a balloon catheter. Sciscione et al. randomised 111 women to outpatient vs inpatient balloon catheter and found no differences between the groups in their primary outcome (change in Bishop score, a clinical assessment of cervical ripening) or secondary outcomes [11]. There were no adverse events or maternal morbidity in this small study. Women in the outpatient group spent 10 fewer hours in hospital. An unanticipated finding was the suggestion that fewer women in the outpatient group needed a caesarean section (29% vs 43%, RR 0.67 (95% CI 0.41–1.10)). The authors suggested that this may be attributed to clinician and patient perception of a longer IOL process in the inpatient group, which might have led to an earlier diagnosis of ‘failed induction’ in the inpatient group. The authors of this Cochrane review called for more trials examining IOL in outpatient settings to assess its safety and effectiveness.

There may be benefits for women to undergo balloon-catheter induction as an outpatient. Henry et al. randomised 101 women in an Australian tertiary hospital to outpatient balloon catheter vs inpatient PGs to assess feasibility, clinical effectiveness and acceptability [12]. Women randomised to outpatient balloon catheter were less likely to achieve vaginal birth within 12 h of admission (28% vs 53%, *p* = 0.01); however, they had comparable rates of caesarean section (34% vs 29%, *p* = 0.6). They spent 11 fewer hours in hospital, had less discomfort (26% reported feeling a lot of discomfort vs 58%, *p* = 0.03) and more hours of sleep (5.8 vs 3.4, *p* < 0.01), felt more able to relax (*p* = 0.01) and to rest (*p* = 0.01), and were more likely to choose this method of IOL again (65% vs 42%, *p* = 0.03). Two other trials in Canada and Australia also show women’s preference for, and satisfaction with, outpatient management [13, 14].

The authors of many of the above studies concluded that a large study was needed to investigate the safety and effectiveness of outpatient balloon-catheter induction. We chose the comparator of inpatient induction with PGE2 because this is the most common method of cervical ripening in NZ (which would facilitate participation in the study). Moreover, due to the 5% risk of uterine hyperstimulation, we felt that it would be safer to keep women in hospital for monitoring throughout (also usual care in most hospitals in NZ).

A search of the ANZCTR identified one registered RCT answering the same research question, with a different primary outcome (ACTRN12614000039684). This trial is being led by [name] in Australia, and the two principle investigators (PIs) have been in regular communication during the progress of both trials.

### Aim

To assess the clinical effectiveness, safety, and cost-effectiveness for mothers and babies of outpatient IOL commencing with a balloon catheter vs inpatient IOL with vaginal PGE2.

### Primary hypothesis

Our primary hypothesis is that women undergoing outpatient IOL with balloon catheter will have a lower caesarean section rate, compared to women having inpatient IOL with vaginal PGE2.

### Secondary hypotheses

Our secondary hypotheses are that outpatient balloon-catheter IOL will not result in increased adverse events for mother or baby; that outpatient balloon-catheter IOL will be associated with increased satisfaction; that outpatient balloon-catheter IOL will be associated with increased staff satisfaction; and that outpatient balloon-catheter IOL will be more cost-effective compared to inpatient IOL with vaginal PGE2.

## Methods/design

### Design

This is a multi-centre, randomised controlled superiority trial.

### Setting

Ten public hospitals around NZ are currently participating in the OBLIGE trial. These are Auckland, Tauranga, Whakatane, North Shore, Waitakere, Waikato, Wellington, Hawkes Bay, Taranaki, and Hutt Valley Hospitals. These hospitals serve urban, regional, and rural areas, and account for 50% of all women giving birth in NZ [3]. The number of women giving birth per year varies from 1514 in Taranaki to 7557 at North Shore/Waitakere [3].

### Characteristics of participants

The target population is pregnant women who develop one or more obstetric risks or complications where expedited birth by IOL is recommended by their clinician.

Women included in the study are pregnant women with a live singleton baby in a cephalic presentation; planning IOL at ≥ 37 weeks’ gestation, intact membranes, normal cardiotocography (CTG), Bishop score < 7, able to remain within 1 h of hospital and to have with them someone who can speak sufficient English to communicate with the hospital midwife on the telephone. A vaginal assessment of the cervix is required to establish the Bishop score, and a CTG also needs to be performed, in order to fully assess eligibility.

Women excluded from the study are women who have undergone previous caesarean; major fetal congenital anomaly; suspected fetal growth restriction; and maternal or fetal condition where the clinician feels that outpatient care would be contraindicated.

### Intervention and comparison

#### Outpatient balloon catheter

The hospital clinician will perform a speculum or vaginal examination (clinician preference) and place the single-balloon Foley catheter through the cervix to above the internal cervical os. The balloon will be inflated with 50 mL sterile saline and the catheter secured to the thigh with slight tension. The woman does not need a routine CTG after placement, unless there is clinical concern or to comply with local protocol. The woman will be asked to rate her discomfort with balloon-catheter placement on a numeric pain rating scale (NPRS) of 0 (no pain) to 10 (worst possible pain).

Before discharge from the unit, the woman will receive detailed verbal information about what to expect, to return to the hospital at any time if she has spontaneous rupture of membranes, contractions, bleeding or reduced fetal movements, and to contact the hospital midwives if concerned. The woman will also receive the OBLIGE written pamphlet on the outpatient balloon catheter with instructions to return to the unit at a specified time, 18–24 h after balloon-catheter placement.

From the time of return to hospital, the woman will remain an inpatient. The hospital clinician will perform a CTG and an ARM. The woman will be asked to rate her discomfort with ARM on a NPRS of 0 (no pain) to 10 (worst possible pain). If ARM is not possible, then the woman will receive PGs (alternative/second method of cervical ripening). Timing of ARM will occur according to clinical prioritisation and acuity in the unit, as for any women in the unit undergoing IOL.

#### Inpatient prostaglandins

The hospital clinician will place either a PGE2 gel (Prostin) or controlled-release pessary (Cervidil) in the vagina. Either method of administration is appropriate (hospital preference). The woman will be asked to rate her discomfort with PG placement on a NPRS of 0 (no pain) to 10 (worst possible pain). The woman does not need a routine CTG after placement, unless there is clinical concern, or to comply with local protocol. After 6 h (for gel) or 12–24 h (for pessary), the hospital midwife will perform a CTG, followed by an ARM. The woman will be asked to rate her discomfort with the ARM on a NPRS of 0 (no pain) to 10 (worst possible pain). If ARM is not feasible due to a low Bishop score, they will either place another PG or switch to second method. The Bishop score should be documented with each exam. Every PG should be prescribed on the National Medication Chart.

The assessment and administration of PG will be repeated regularly (not < 6 h for gel; not < 12 h for pessary) until ARM is possible, or the woman is established in labour or spontaneous rupture of membranes occurs, or the clinical team prefers to change to the second/alternative method, or to a maximum of six doses for gel or two doses for pessary. The timing and dose of each follow-up PG dose can be at the discretion of the clinical team. The date and time of the first and last PG will be documented. Whenever the woman starts to feel regular strong painful contractions, the midwife will perform a CTG. If ARM is still not possible, then the woman will be offered a balloon catheter (second method of cervical preparation) and remain an inpatient. However, if neither ARM nor balloon-catheter insertion is possible, then a senior clinician will decide how to proceed.

#### Discontinuing allocated intervention

Based on previous trials, we anticipate that some women will request removal of the catheter due to discomfort. Some women after randomisation may choose not to continue to participate in the trial for other reasons. If a participant withdraws, we will seek her consent to continue to have her data collected from her clinical notes.

#### Adherence to intervention protocols

Members of the research team at each hospital will be available to answer questions about the study protocols and reinforce the importance of adhering to the study protocols. Each hospital will embed reminders into their usual protocols and medical records.

#### Relevant concomitant care and interventions

Following ARM or spontaneous rupture of membranes, in the absence of spontaneous onset of strong regular contractions within 1–2 h, intravenous infusion of oxytocin will be started and titrated to the contractions, according to local hospital protocol. It should not be started < 6 h from insertion of the last PG gel or < 12 h from last PG pessary (if applicable). Continuous CTG monitoring is recommended whilst on oxytocin. Clinical care to participants will be provided by multiple clinicians throughout their induction, labour, birth, and post-partum. It is up to the discretion of the clinician if, during a cervix assessment, they also perform membrane sweeping. Established labour (defined for the purposes of this study as regular, strong, painful contractions and cervix dilated 4 cm or more) will be managed by the participant’s clinicians as per local protocol. Analgesia will be administered according to maternal request as per local practice. Additional care for study participants outside of routine labour and birth care is the collection of paired cord-blood samples. Each hospital has committed to not offer outpatient balloon-catheter IOL outside of this study for the duration of the study.

### Primary outcome

Caesarean section:

the proportion of participants who give birth by caesarean section.

### Secondary outcomes

*NOTE: all outcomes listed are as recommended for an IOL study by COSIOL* [15].

Maternal:

### Measured at time of induction of labour

For balloon catheter only:
Duration in situ (time in hours will be calculated at the end of the study, based on times recorded by the staff member (from time of placement to time of removal/falling out)Balloon catheter removed or fell out, measured by staff member when patient readmitted to hospitalEarly unplanned return to hospital (yes/no) and reason, collected by staff member when patient readmitted to hospitalFor PGs only:
Total number of doses given (compare median number between groups)For both methods:
Discomfort during placement (NPRS, from 0 (no pain) to 10 (worst possible pain)), asked by staff member to the patient using a pictorial of the pain scale, measured in the first few minutes after placementNeed for second method of cervical ripening (proportion of participants who need a second method, yes/no)Need for ARM (proportion of participants who need ARM, yes/no)Discomfort during ARM (NPRS, from 0 (no pain) to 10 (worst possible pain), asked by staff member to the patient using a pictorial of the pain scale, measured in the first few minutes after ARM

### Measured at time of birth

Proportion of participants who had use of oxytocin infusion and at what cervical dilation it started (median score, from 0 to 10)Uterine hyperstimulation (yes/no)Proportion of participants who had use of epidural anaesthesia and at what cervical dilation it was placedClinical diagnosis of chorioamnionitis (yes/no)Proportion of participants who had a clinically significant antepartum haemorrhage after start of IOL – cause, timing, and if associated with abnormal CTGFetal blood sampling (lactate or pH) performed during labour (proportion of participants who had this done) and results (mean measurement)Mode of birth (proportion of participants who had spontaneous vaginal, assisted vaginal or caesarean section)Proportion of participants who had a vaginal birth within 24 h of start of IOLIf caesarean section, reason and at what cervical dilation (mean score, from 0 to 10)Proportion of participants who had failed IOL (defined for the purposes of this study as caesarean section performed at < 4 cm)Uterine rupture (yes/no)Non-cephalic presentation (yes/no)Cord prolapse (yes/no)Stillbirth (yes/no)

### Measured post-partum before hospital discharge

*Post-partum haemorrhage* (proportion of participants in each of three subgroups: 500–999 mL, 1000–1499 mL, 1500 mL or more), red blood cell transfusion (yes/no), transfer to theatre (yes/no)Clinical diagnosis of *post-partum endometritis* (yes/no)*Admission to intensive care* unit (primary diagnosis, outcome) (yes/no)

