### Sample size calculation

At Auckland Hospital in 2015, the caesarean section rate in women who had undergone IOL (excluding women who had undergone previous caesarean section) was 24.8%, almost all of these women were induced using PGs [16]. In the small trial of outpatient vs inpatient balloon-catheter IOL, the risk of caesarean section rate decreased from 43 to 29% (a relative reduction of 32%) [11]. In order to detect a clinically meaningful change in risk of caesarean section rate from 24.8 to 18.8% (a relative risk reduction of 24%), with 80% power and a two-sided type 1 error of 0.05, we require a sample size of 743 women for each study group. Adding a continuity correction, the total sample size required is 1552 women.

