### Statistical analysis

Baseline demographic and clinical characteristics will be described for each study group. Analyses will follow the principle of intention-to-treat; participants will be analysed according to the assigned intervention group at randomisation. Multivariable models will control for potentially confounding variables and include hospital site and parity. Binary endpoints will be analysed using logistic regression to estimate odds ratios for the intervention. Continuous outcomes will be modelled using generalised linear models to estimate any changes in outcomes between the two interventions. A *p* value of 0.05 will be considered as statistically significant. We recognise that there are a number of secondary outcomes; as they are secondary outcomes we will report *p* values without correction, which would be overly conservative. Missing data will not be imputed.

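### Post-partum haemorrhage is specified only as three exclusive blood-loss bands; cumulative thresholds would give comparisons ordered by harm and, below 1500 mL, better powered, at almost no cost

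*Protocol article*

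**What the plan says.** In the protocol article, the list of outcomes measured post-partum before hospital discharge gives post-partum haemorrhage as the "proportion of participants in each of three subgroups: 500–999 mL, 1000–1499 mL, 1500 mL or more". Red-cell transfusion and transfer to theatre follow as separate yes/no items. No cumulative blood-loss threshold appears there or elsewhere among the outcomes.

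The Statistical analysis section names two methods. "Binary endpoints will be analysed using logistic regression to estimate odds ratios for the intervention", and "Continuous outcomes will be modelled using generalised linear models". Multivariable models are to include hospital site and parity. No method is named for an outcome with several ordered categories. Secondary outcomes are tested without correction for multiplicity.

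Haemorrhage is relevant to a stated hypothesis. The Introduction lists it among the complications that are more frequent after induction than after spontaneous labour, and the Secondary hypotheses section expects that "outpatient balloon-catheter IOL will not result in increased adverse events for mother or baby".

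**The concern.** A woman who loses 1600 mL belongs to the top band only. If each band is compared separately by logistic regression, the comparison group for the 500–999 mL band holds both women who lost less than 500 mL and women who lost 1000 mL or more. The same mixing affects the 1000–1499 mL band. A larger odds ratio in these two bands does not simply mean more harm, nor a smaller one less.

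In addition, a general rise in blood loss is spread over three comparisons, each of which sees only part of it. Where the hypothesis is that adverse events do not increase, weak comparisons favour finding nothing, which is the less safe direction for a harm.

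Crude totals for 500 mL or more and 1000 mL or more can be had by adding the bands. An adjusted odds ratio, its interval and its p value cannot: they need an endpoint defined in its own right. If that endpoint is added after the data are seen, it is post hoc.

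**Working it through.** **The plan's own figure.** The Sample size calculation section uses 24.8% against 18.8%, 80% power and two-sided 0.05.

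- n = [1.96·√(2·0.218·0.782) + 0.8416·√(0.248·0.752 + 0.188·0.812)]² / 0.06² = 742.2, so 743 per group, as stated.
- Continuity correction: (743/4)·[1 + √(1 + 4/(743·0.06))]² = 776 per group, 1552 in total, as stated.

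This figure concerns caesarean section only. It is used below for the arm size (776, assuming complete data).

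**Inputs that the documents do not give.** No blood-loss distribution or haemorrhage rate is stated. Assumed: log-normal loss, log-SD 0.6, control median m = 350, 450 or 550 mL, and every loss multiplied by 1.15 in the other arm.

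**Formulas.**
- P(loss ≥ x) = 1 − Φ[(ln x − ln m)/0.6]; a band is the difference of two such terms.
- OR = [p1/(1 − p1)] / [p0/(1 − p0)].
- Power (unadjusted Wald test) = Φ( |ln OR| / √[1/(776·p0(1 − p0)) + 1/(776·p1(1 − p1))] − 1.96 ).

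**One case in full, m = 450 mL.**
- Loss of 500 mL or more: 43.03% against 52.29%. OR = 1.45, ln OR = 0.3725, standard error = 0.1021, ratio 3.65, power Φ(1.69) = 95%.
- 500–999 mL band: 33.87% against 38.67%. OR = 1.23, ln OR = 0.208, standard error = 0.1058, ratio 1.97, power Φ(0.01) = 50%.

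**All cases: OR (power).**

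| Endpoint | m = 350 | m = 450 | m = 550 |
|---|---|---|---|
| 500–999 mL | 1.35 (74%) | 1.23 (50%) | 1.11 (18%) |
| 1000–1499 mL | 1.59 (42%) | 1.46 (53%) | 1.37 (54%) |
| 1500 mL or more (same in both definitions) | 1.87 (23%) | 1.73 (43%) | 1.64 (62%) |
| 500 mL or more | 1.47 (94%) | 1.45 (95%) | 1.46 (95%) |
| 1000 mL or more | 1.66 (58%) | 1.56 (78%) | 1.51 (88%) |

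No single band reaches the power of the 500 mL or more endpoint in any case. The 1000 mL or more endpoint beats both upper bands each time. All band odds ratios stay above 1, so a general upward shift weakens the signal without reversing it.

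**When a lower band does reverse.** This needs more women to leave the band upwards than enter it from below. Assumed control rates of 20/6/2% in the three bands against 16/8/4% give:
- Bands: OR 0.76, 1.36 and 2.04.
- Cumulative: 28% against 28%, OR 1.00; 8% against 12%, OR 1.57; 2% against 4%, OR 2.04.

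Over control rates from 15/4/2% to 25/8/4%, with 2 to 6 points moved out of the lowest band and split equally between the two upper bands, the lowest-band OR runs from 0.56 to 0.90 while the 1000 mL or more OR runs from 1.19 to 2.14.

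**A single ordinal test instead.** In the 20/6/2% against 16/8/4% example, a rank test over the four ordered categories (a stand-in for a proportional-odds model) has only about 8% power, because the movement is confined to women already at 500 mL or more.

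**The case against.** A reader might infer that the plan scores each woman yes or no in every band, so that a 1600 mL bleed counts as no haemorrhage in two of them and worse bleeding shows up as less. The documents do not support that. The transfusion and theatre items are marked yes/no; the bands are not. The wording also fits one categorical outcome reported by severity, as mode of birth is. All three bands would be reported together, and the open-ended top band captures the worst bleeds. In the example with the reversed lowest band, the three odds ratios side by side (0.76, 1.36, 2.04) show the move to severe bleeding, whereas the 500 mL or more endpoint alone, at 1.00, does not. The reversal is absent from the log-normal calculations.

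The power contrast also needs care. The lowest figure, 18%, comes from the 550 mL median, which puts 56% of controls at 500 mL or more, a rate that nothing in the documents supports. At medians of 350 and 450 mL the same band has 50–74%. The protocol claims no power for haemorrhage, which is one of many secondary outcomes. Finally, modelling of a multi-category outcome may be settled in an analysis plan that is not shown.

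Most of this stands and limits the point. What remains is that the article does fix the summary measure, that the measure contains no cumulative endpoint, and that adding crude bands does not supply an adjusted comparison.

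**Conclusion.** The point holds as a minor one: a cheap improvement to one secondary safety outcome. Haemorrhage is defined only by exclusive bands. If those bands are compared one by one under the stated logistic model, the two lower odds ratios are not ordered by harm, and the signal is split over weaker tests.

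Under the assumed 15% rise, power is 18–74%, 42–54% and 23–62% for the three bands, against 94–95% for 500 mL or more and 58–88% for 1000 mL or more. These figures depend on the assumed log-normal shape, medians and shift, on 776 complete records per arm, and on an unadjusted test.

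The stronger conclusion, that worse bleeding would appear as less haemorrhage, applies only to a lower band read alone after a particular movement from that band to higher ones. It does not describe the outcome as a whole. The 1500 mL or more result is identical under either definition, and the primary outcome and sample size are untouched.

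**What to change.** In the list of outcomes measured post-partum before discharge, define haemorrhage by cumulative thresholds: loss of 500 mL or more, 1000 mL or more, and 1500 mL or more. Analyse each with the planned logistic model adjusted for hospital and parity. Keep the three bands as a descriptive table, so that a shift in severity among women at 500 mL or more stays visible.

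Do not replace the thresholds with a single proportional-odds model, which can miss a shift confined to severe bleeding.

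The cost is one line of outcome wording; the same blood-loss data serve. The small downside is that the thresholds overlap, so their p values are correlated and should not be read as three independent findings. If the analysis plan already defines these thresholds, the outcome list need only be brought into line with it.
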